### Time of the refill

The time required for the procedure will be recorded from two perspectives. First, the time for the refiller will be measured: for home-based refills, this includes the duration from entering the patient's house until departure. For hospital-based refills, it covers the time spent in the patient's room in the outpatient clinic. Second, the time required for medical supervision will be recorded: for home-based refills, this includes the full duration of the online consultation. For hospital-based refills, it includes the time the physician spends in the outpatient clinic with the patient.

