| Description                                       | 
The experimental intervention consists of two pump refills for each patient, administered at home. The procedure itself will remain unchanged; however, instead of receiving it at the hospital, the refills will be conducted in the patient's home environment. A researcher will visit each patient at their home; this will be performed under remote control.
 
In the hospital pharmacy of UZ Brussels, the day before the refill procedure, a sealed box will be prepared for every patient. This will be stored at room temperature. The prescription and medication label will be double-checked by the hospital pharmacist and the refill team.
 
Once the researcher arrives at the patient's home, the first step will be to set up the telemonitoring system. Both the researcher at home and the researcher in the hospital will log in to a secure web connection. The researcher at home wears smart glasses, enabling full remote visual and audio monitoring. The researcher at the hospital will have the same view as the researcher at the patient's home. The
 |

|                                         |                                                                                                                                                                                                                                                                                                                                                                                                                                                                                                                                                                                                                                                                                                                                                                                                                                                                                                                                                                                                                                                                                                                                                                                                                                                                                                                                                               |

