|                                         | 
home researcher will then verbally confirm the pump settings and cross-check the medication label with the prior pump information. A final check is made when the researcher at the patients' home presents the medication label directly to the researcher in the hospital. After completing all verifications, the sterile refill procedure will be carried out again under remote supervision. The researcher at home will be a predoctoral neurosurgical resident, the researcher at the hospital will be a predoctoral researcher schooled in biomedical sciences.
 
Following the refill, a post-refill evaluation using an ultrasound device (Clarius C3 Scanner, Vancouver, Canada) will be performed to confirm that the pump was correctly refilled and that no subcutaneous drug injection occurred. Once this confirmation is secured, the remote connection will be terminated (Fig. 2, section 15). If the procedure cannot be carried out in a clean and sterile manner at the patient's home (e.g., due to poor hygiene or inadequate general body care), the home refill attempt will be considered unsuccessful. In that case, the procedure will be rescheduled and performed at the outpatient clinic within the same week. After the refill procedure, we suggest the presence of a caregiver during approximately 12 hours.
 |

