| Intervention team                | 
The intervention team consists of two main people: the researcher in the hospital and the researcher at home. The last one is responsible for the refill intervention. This person will go to the patient's home and perform the procedure.
 
The researcher, who will be at VUB/UZB, is the connection and will remain in close contact with the researcher during the refill at home.
 
This team will be supervised by the PI, [name] and indirectly supervised by the outpatient, treating physician of the patient.
                                                                                                                                                                                                                                                                                                                                                                                                                                                                                                                                                                                                                                                                                                                                                                                                         |

| Control intervention |                                                                                                                                                                                                                                                                                                                                                                                                                                                                                                                                                                                                                                                                      |

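### Medical-supervision time sets a remote researcher's call at home against the operating physician's minutes in hospital, so it cannot show whether home refills save or cost physician time

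*Protocol*

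**What the plan says.** Protocol section 6.3.2, Time of the refill, sets up two clocks.

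- The first times the refiller: from entering to leaving the house at home, and the time in the patient's room in hospital.
- The second is introduced with "Second, the time required for medical supervision will be recorded". Its home rule is "for home-based refills, this includes the full duration of the online consultation". Its hospital rule is that "it includes the time the physician spends in the outpatient clinic with the patient".

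Section 9.2 describes the staff.

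- On the home connection: "Both the researcher at home and the researcher in the hospital will log in to a secure web connection". The smart-glasses row likewise describes a channel between two people, both researchers.
- On who they are: "The researcher at home will be a predoctoral neurosurgical resident", and "the researcher at the hospital will be a predoctoral researcher schooled in biomedical sciences".
- Setting up the connection is the first task on arrival. It is ended after the ultrasound check that follows the refill.
- The team is supervised by the principal investigator and "indirectly supervised by the outpatient, treating physician of the patient".
- For the control intervention, the physician carries out the refill.

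The protocol summary lists consultation time among the secondary outcomes on which the two arms are compared. The documents give no expected duration for any of these times.

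**The concern.** One label covers two different things. At home it holds the length of a call whose hospital end is staffed by a researcher with a biomedical sciences background. In hospital it holds the minutes of a physician, who is also the person doing the refill. The supervision at home that is explicitly tied to a physician, the indirect supervision by the treating physician, has no clock, and neither has supervision by the principal investigator.

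A difference reported under this label would mix staff category with location. Section 5.1.5 names specialist involvement as a factor in the economics of hospital-at-home care, so readers will look to this outcome to see whether home refills save or cost physician time. It cannot tell them. This is a data-capture rule: minutes not noted at the refill cannot be recovered by a later analysis plan.

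**Working it through.** There is no stated figure to reproduce. The check sets the definition against the staffing and then works out the signs.

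**Whose minutes are recorded**

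| | Home | Hospital |
|---|---|---|
| Refiller clock | Resident, entry to departure (H) | Physician, time in the patient's room |
| Medical-supervision clock | Whole call, with the researcher at the hospital end (C) | Physician, time with the patient (P) |
| Principal investigator or treating physician overseeing the home refill | Not timed (u) | Not applicable |

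The call starts after arrival and ends before departure, so H ≥ C. In hospital the physician appears on both clocks.

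**Differences, home minus hospital**

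- Recorded: C − P.
- Supervising-physician time, resident not counted as a physician: u − P. As the protocol describes the call, no physician joins it as supervisor. With other input taken as zero this is −P.
- Physician time, resident counted as a physician: H + u − P, or H − P with u = 0.

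**When the recorded sign is opposite (u = 0)**

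- Resident not counted: C − P > 0 while −P < 0, so whenever C > P.
- Resident counted: C − P < 0 while H − P > 0, so only when C < P < H. When C > P, H − P is positive too and the signs agree.

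**Error in minutes (u = 0)**

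- Resident not counted: (C − P) − (−P) = C, the whole call.
- Resident counted: (C − P) − (H − P) = −(H − C), the part of the visit outside the call.

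**Illustration.** All durations are assumptions: P 15 to 45, C 15 to 60, H 10 to 20 minutes longer than C.

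| P | C | H | Recorded C − P | Resident not counted, −P | Resident counted, H − P | Opposite sign to |
|---|---|---|---|---|---|---|
| 15 | 20 | 30 | +5 | −15 | +15 | resident not counted |
| 20 | 30 | 40 | +10 | −20 | +20 | resident not counted |
| 45 | 60 | 70 | +15 | −45 | +25 | resident not counted |
| 20 | 15 | 25 | −5 | −20 | +5 | resident counted |
| 30 | 20 | 40 | −10 | −30 | +10 | resident counted |
| 30 | 15 | 25 | −15 | −30 | −5 | neither |
| 45 | 30 | 40 | −15 | −45 | −5 | neither |

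Over these ranges the error is +15 to +60 minutes per home refill if the resident is not counted, and −10 to −20 minutes if the resident is.

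**Untimed input.** With C > P and the resident not counted, the signs stay opposite as long as u < P. If u is a physician's share s of the call, that means s < P/C: 20/30 = 0.67 or 20/40 = 0.50.

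**Records affected.** 82 × 2 = 164 home refills at the minimum sample size. The sample size section allows for 20% loss. If every lost patient had no home refill, 164 × 0.8 = 131.2 would remain, so about 131 to 164.

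**The case against.** A reader might infer that no physician takes part in home refills and that the recorded difference reverses the true physician-time difference. The documents do not support either. The home refiller is a neurosurgical resident, who may well be medically qualified and is on the call throughout. If the resident counts as a physician, a call longer than the hospital visit causes no reversal. Without durations, nobody can say whether C exceeds P. It also remains an inference that the hospital-end researcher is not a physician: the protocol gives a background in biomedical sciences and does not rule out a medical qualification. All of this stands, and it limits the point to what the variable cannot show.

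A second objection is that the label names a supervisory function, not physician time, and that at home the supervision is the call. This does not rescue the comparison. In hospital the recorded minutes belong to the physician who does the refill, so supervisor minutes are still set against operator minutes.

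Third, the two home clocks already hold the resident's and the remote researcher's minutes, so much of a split by role could be rebuilt. That is right, and it makes the change cheap. It does not supply the untimed oversight, correct the label, or settle how the resident is classed.

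Finally, the health expenditure and health economic sections build costs from claims data, telephone interviews and national tariffs, and do not name recorded refill time as an input. So no error in the cost-effectiveness ratios is shown.

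**Conclusion.** The point holds as a definition that is not like for like in one secondary outcome. Followed as written, the plan would report as medical supervision a contrast between a remote researcher's call and the operating physician's own minutes, with physician oversight of home refills left out. That contrast cannot show physician time saved or spent.

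Size and direction are unknown. Sign reversal is possible under either classing of the resident, but under opposite conditions, and the protocol has no figures to decide between them. The conclusion rests on reading the call as section 9.2 describes it, with two researchers and no physician joining as supervisor. The primary comfort outcome and N = 82 are unaffected. The change is worth making before more refills are timed.

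**What to change.** Reconcile the Time of the refill definition with the home procedure, Intervention team and control rows of section 9.2, so that it is clear whose minutes are recorded at each location. This concerns what is recorded and how it is labelled, not who should supervise.

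- Record minutes per staff role for every refill: the refiller (resident at home, physician in hospital, counted once); the remote researcher (call duration); and any principal investigator or treating-physician minutes spent on that home refill.
- State whether the resident is classed as a physician for this outcome.
- Compare role-specific and total staff minutes by location.
- Do not report the researcher's call as medical supervision.

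The cost is one or two extra fields on the refill form and a wording change. Physicians consulted about a home refill must note their minutes, and brief contacts may be under-recorded. No extra visits or patients are needed.

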### Safety

Patients will evaluate the overall safety of the procedure using a seven-point Likert scale. In addition, both the researchers (at home and at the hospital) will assess safety on three levels: (1) overall perceived safety of the procedure using a seven-point Likert scale; (2) environmental safety, assessed through an open-ended question addressing any situations perceived as unsafe; and (3) the ability to perform the procedure in a clean and sterile manner, also evaluated via an open-ended question. Between two and twelve hours after the refill at home, the researcher at the hospital will contact all patients by phone to assess the occurrence of any adverse events.

### Health expenditure

Expenditures related to in-hospital care will be extracted from hospital claims data. All other healthcare-related costs will be gathered through telephone interviews with patients, conducted four weeks after the first and second medication refills. During these calls, researchers will ask patients whether they have had any medical consultations, hospital admissions, adverse events, changes in medication, or incurred any additional healthcare costs.

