#### Need for head-to-head comparison and economic evaluation

Systematic reviews remain unclear about the economic benefit of HAH programs (28,39). To comprehensively assess the economic impact of HAH, several factors should be considered, including the involvement of specialists, the feasibility of multi-session home treatments, the hospital's location and financial status, as well as the geographical distribution of patients (40). However, advances in technology have paved the way for the inclusion of telemedicine in surgery and acute management (41,42). The initial development focused on telepresence, enabling the remote operating site to be experienced in a natural and immersive way, thereby creating a sense of presence. Ongoing research continues to demonstrate the effectiveness of telemonitoring and remote telesurgery, where an experienced surgeon can conduct procedures from a distance, through for example robots (43). In our PoC study in performing pump refills at home, both the physician and specialist nurse conducted refill procedures at home. This application fits well with the goals of telemonitoring and telemedicine, making it useful for remote pump refills.

A proper economic evaluation to determine the cost effectiveness as well as a full evaluation of patient-reported outcomes concerning health-related QoL and emotional and psychological well-being have not yet been conducted. This is, however, crucial for further implementation of remote refill procedures in clinical practice and seems to be the final hurdle that must be taken to provide the HAH option to patients. A utility score of 0.4523 for a successful refill at the hospital and of 0.4658 for an intrathecal refill procedure at the patient's home is expected (assumption 3% higher) (44–49). We conducted a back-of-the-envelope calculation that resulted in an incremental cost effectiveness ratio (ICER) of €32.255/quality-adjusted life year (QALY) and €12.148/QALY on a 10-year time horizon for 4 versus 6 IDD refills per year respectively (depending on the exact dose of medication 4 or 6 refills per year are needed), demonstrating that refills at home have the potential to be cost-effective.

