### Endpoints

During the baseline assessment, patients are asked to provide information on their demographic and socio-economic background—including sex, age, marital status, ethnicity, years of education, highest

obtained degree, employment status, income, whether or not they receive home care or have an informal caregiver, and household composition — as well as clinical baseline data, such as the year of pump implantation, medication, indication for having an IDD pump. The general data protection regulation principle of data minimization and proportionality will always be considered.

Further, patients will receive questionnaires related to our primary and secondary outcome measures, as described below. Following this initial assessment, patients will be randomized. The randomization list will be created in R, whereby each patient will receive two refills in the outpatient clinic and two refills at home in a randomized order. After each refill, all baseline outcome measures will be reassessed. In addition, secondary outcomes such as patient satisfaction and preference, telemonitoring quality (applicable only for home refills), and safety will be evaluated during follow-up assessments. Health expenditure data will be collected through phone calls. The researchers will call each patient four weeks after the first refill and four weeks after the second refill. Questions will be asked concerning health-economic aspects. These questions will be based on the following variables: consultations, adverse events, hospitalizations, medication, other health-related costs. For more details concerning these questions, we refer to the health economic telephone interview. To prevent test order effects, the test order of the self-reported measures will be randomized for each individual patient at each assessment. After the fourth refill patients will be asked to complete a Discrete Choice Experiment (DCE). Table 1 (section 15) provides an overview of the outcomes, the timing of assessments, and the designated respondents for each questionnaire.

The self-reported measures will be completed online via REDCap (Research Electronic Data Capture) to enhance study feasibility and ensure data security. For participants who are unable to complete the questionnaires online, or in cases where internet connectivity is limited, paper-based versions of the questionnaires will be available.

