### *Health economic analysis*

A within-trial health economic evaluation will be conducted to assess the cost-effectiveness of home-based intrathecal pump refills compared to standard outpatient clinic refills. The analysis will include all participants, covering the period up to just before the third refill procedure. Each participant will receive one refill at home and one in the outpatient clinic, with a follow-up period of approximately 2–3 months between the refills.

The analysis will follow the intention-to-treat principle (79). Data on resource use will be collected through telephone interviews, as described in the outcome section ‘health expenditure’. The valuation of resource use will be based on official Belgian national tariffs.

Health outcomes will be assessed in two ways:

1. Percentage increase in comfort, as measured by the General Comfort Questionnaire, is the trial’s primary outcome.
2. Utility values, derived from EQ-5D questionnaires and converted using Belgian population-based value sets, in line with national health economic guidelines (55).

The outpatient refill procedure will serve as the control group. Any missing data will be addressed before analysis using appropriate methods for handling incomplete health economic data (79).

Cost differences between the two groups will be analyzed using generalized linear models. The Modified Park Test will guide the selection of the appropriate model specification (80). The main result will be the Incremental Cost-Effectiveness Ratio (ICER) (81), calculated with the estimation:

$$ICER = \frac{(\text{incremental cost})}{(\text{percentage increment in functioning})}$$

and

$$ICER = \frac{(\text{incremental cost})}{(\text{incremental QALY gained})}$$

To account for uncertainty, probabilistic sensitivity analysis will be conducted (79). Non-parametric bootstrapping will be used to assess variability in cost and outcome estimates. These results will be illustrated using Cost-Effectiveness Acceptability Curves (CEACs), showing the probability that the intervention is cost-effective at various willingness-to-pay (WTP) thresholds. All results will be reported in accordance with the Consolidated Health Economic Evaluation Reporting Standards (CHEERS) guidelines (82).

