## Tables and Figures

| What? | Patient comfort *                                                                                                                                                    | QoL *        | Pain Intensity * | Pain interference * | Stress *          | Anxiety * | Self-efficacy * | Burden caregivers * | Patient satisfaction | Tele-monitoring quality** + time | Safety                                                    | Health expenditure *** | Patient preference    |
|-------|----------------------------------------------------------------------------------------------------------------------------------------------------------------------|--------------|------------------|---------------------|-------------------|-----------|-----------------|---------------------|----------------------|----------------------------------|-----------------------------------------------------------|------------------------|-----------------------|
| How?  | GCQ                                                                                                                                                                  | MQOL + EQ-5D | VAS              | PROMIS              | Sarsted t AG & Co | STAI      | GSE             | ZBI                 | Likert-scales        | Likert-scales + time expenditure | Overall safety + environmental safety + sterile procedure | Phone calls            | Multiple choice + DCE |
| When? | At baseline * and after each intrathecal pump refill (** only applicable for refills at home)
***Four weeks after first refill and four weeks after second refill |              |                  |                     |                   |           |                 |                     |                      |                                  |                                                           |                        | After last refill     |
| Who?  | Patient                                                                                                                                                              | Patient      | Patient          | Patient             | Salivary sample   | Patient   | Patient         | Caregiver           | Patient              | Researchers                      | Patient + researchers                                     | Patient                | Patient               |

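### Out-of-hospital costs have no stated source from four weeks after the second refill to the third, although the within-trial economic evaluation covers that period

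*Protocol*

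**What the plan says.** Three places in the protocol give the same schedule for the cost interviews. Section 6.3 (Endpoints): "The researchers will call each patient four weeks after the first refill and four weeks after the second refill". Section 6.3.2 (Health expenditure): "All other healthcare-related costs will be gathered through telephone interviews with patients, conducted four weeks after the first and second medication refills". The footnote of Table 1 (section 15): "Four weeks after first refill and four weeks after second refill". No further cost interview is described.

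Section 6.3.2 splits the sources. "Expenditures related to in-hospital care will be extracted from hospital claims data"; everything else comes from the calls.

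Section 10.4.3 (Health economic analysis) sets the period of the within-trial evaluation as "covering the period up to just before the third refill procedure", each patient having one home and one outpatient refill, "with a follow-up period of approximately 2–3 months between the refills". The same section takes resource use from the telephone interviews and makes the incremental cost-effectiveness ratio (ICER) the main result.

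The protocol does not state how far back each call looks. Section 6.3 refers to a separate interview form for the details of the questions.

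**The concern.** The collection schedule and the analysis period are both fixed in the protocol, and they do not match. The last cost question is put four weeks after refill 2, while the evaluation continues until just before refill 3. Consultations, medication and other costs outside hospital in the remaining weeks are asked about for no patient.

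The ICER would then combine truncated out-of-hospital costs with a period declared to run to refill 3. If within-trial costs feed the lifetime Markov model, the truncation carries over. A later analysis plan cannot supply data that were not collected, and what a patient spent in those weeks becomes harder to recover as time passes.

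**Working it through.** **Inputs**
- Calls at refill 1 + 4 weeks and refill 2 + 4 weeks (sections 6.3 and 6.3.2, Table 1).
- Window: to just before refill 3 (section 10.4.3). Its start is not stated; refill 1 is assumed.
- Interval between refills: about 2–3 months (section 10.4.3). Equal intervals are assumed.
- 1 month = 365.25 / 12 / 7 = 4.348 weeks.

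**Check of the stated interval.** Section 5.1.5 says that "depending on the exact dose of medication 4 or 6 refills per year are needed". 12/6 = 2 months and 12/4 = 3 months, which reproduces the stated 2–3 months.

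**Lengths.** Interval = months × 4.348, so 8.7, 10.9 and 13.0 weeks for 2, 2.5 and 3 months. Window = 2 × interval = 17.4, 21.7 and 26.1 weeks.

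**Gap that exists on any look-back.** Weeks from call 2 to refill 3 = interval − 4. Share of the second interval = 1 − 4/interval.

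**Share of the whole window**, under two possible look-backs:
- Reading A, each call asks only about the time since its own refill: 1 − 8/window.
- Reading B, call 2 asks about the time since call 1: 1 − (interval + 4)/window.

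| Interval | Gap before refill 3 | Share of second interval | Window uncovered, A | Window uncovered, B |
|---|---|---|---|---|
| 2 months | 8.7 − 4 = 4.7 wk | 54% | 9.4 of 17.4 wk = 54% | 4.7 of 17.4 wk = 27% |
| 2.5 months | 10.9 − 4 = 6.9 wk | 63% | 13.7 of 21.7 wk = 63% | 6.9 of 21.7 wk = 32% |
| 3 months | 13.0 − 4 = 9.0 wk | 69% | 18.1 of 26.1 wk = 69% | 9.0 of 26.1 wk = 35% |

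Counting a month as four weeks changes little: A gives 50–67% and B gives 25–33%.

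**A further cost of reading B.** Call 2 would span the end of one location's period and the start of the other's, so items could be assigned to home or hospital only if each is dated. The two periods would also be observed for unequal lengths: 8.7 against 4 weeks, or 13.0 against 4 weeks.

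**Effect on the cost difference**
- Under reading A, if the out-of-hospital cost difference accrues evenly over the interval, the observed part is 4/interval. The understatement factor is 8.7/4 = 2.2 to 13.0/4 = 3.3.
- If the difference falls mainly near the refill, the four-week call captures most of it and the factor is close to 1.

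**The case against.** **The look-back is unstated.** Section 6.3.2 fixes when the calls take place, not the period they ask about. A reader might infer that more than half of the window is unobserved. That holds if each call covers only its own four weeks, which is a natural reading but not a stated one. If call 2 looks back to call 1, the first interval is fully covered and the gap is 27–35%. This objection stands, so the size has to be given as a range.

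**Other records exist.** Adverse events are reported from baseline to the end of the study (section 10.1.1). Section 11.4 provides eCRF pages for concomitant treatments and adverse events, and hospital claims are not tied to the call dates. It would therefore go too far to say that late complications and medication changes go unrecorded. But section 10.4.3 names the interviews as the source of resource use and does not say that eCRF entries will be costed. Those pages are also not described as capturing consultations or other expenses, so they do not close the gap.

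**Missing data will be handled.** Section 10.4.3 promises appropriate methods for incomplete data. These weeks are unasked for every patient by design, so there are no observed values from which to impute them.

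**Costs may fall on the refill day.** The burdens described in section 5.1.4 (transport, caregiver hours) attach to the refill itself. If the cost difference sits there, the schedule loses little of it. This stands, and it is why the 2.2- to 3.3-fold figure is the upper end of a range.

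**No direction is shown.** A reader might infer that the gap flatters one location. The first pair contains one home and one hospital refill in randomized order (section 7.2), and the same call schedule follows both. If the two orders are balanced, the gap does not by itself favour either.

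**Conclusion.** The mismatch is real on any reading. Out-of-hospital resource use from four weeks after refill 2 to refill 3 has no stated costing source, so total costs are understated relative to the declared window. The minimum shortfall, 27–35% of that window, rests on a start at refill 1, equal intervals of 2–3 months and the more generous look-back. The larger share of 54–69% needs the four-week look-back, and the fold-understatement also needs even accrual; the protocol states neither. Directional bias in the ICER is not established.

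The point should be fixed, but it is not critical to the trial. The economic evaluation is the third objective (section 6.2), and the primary comfort endpoint and its analysis are unaffected.

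**What to change.** Keep the two four-week calls and repeat the same cost questions at the existing refill 2 and refill 3 visits, before the refill, covering the time since the previous call. State that each call asks about the time since its own refill. The four contacts then cover both intervals fully and equally, and every item belongs to one location.

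An alternative is to move the two calls to just before refills 2 and 3, each covering the time since the previous refill.

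Either way, write the look-back into the protocol and align sections 6.3, 6.3.2 and 10.4.3 with Table 1. Section 10.4.3 should also state when the window starts.

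The cost is one short form at two visits that take place anyway, or, if the calls are moved, the same number of calls with a recall of 2–3 months instead of four weeks.

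Cutting costs and QALYs back to four weeks after each refill is not a good substitute: Table 1 schedules the EQ-5D at baseline and after each refill, so no utility is measured at week four.
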